#### Direct and indirect cost data collection

We measured all costs at each site using a costing operations manual outlining a standardized multistep process (Additional file 1). Between 2007 and 2011, the principal investigator and a research assistant contacted the site principal investigator and research coordinator at each participating center with the list of variable costs required, who then subsequently contacted the most appropriate individual in each hospital’s accounting, human resources, pharmacy, radiology and laboratory services and blood bank. Standard definitions (per unit of measurement or time, and so on) were created and explained and hospital-specific costs requested for each variable. Where costs were influenced by extra-hospital jurisdictions (such as jurisdictional payer physician costs, unionized employees and reference laboratory costs), these were recorded. In all cases, costs were requested but if only charges were known, then we converted to costs by the institution’s cost-to-charge estimate for that item. Both professional (performance and/or interpretation) and technical costs were recorded for procedures when applicable. We undertook an iterative series of communications until no further data could be gleaned. All data are without patient identifiers and are be maintained in password-protected and encrypted laptop or desktop, in locked offices.

#### Exploring cost variability among sites

To explore variability among centers and countries, cost data will be summarized by means (and standard deviations) and medians (and interquartile ranges) among all sites, and by country for all variables, as per our pilot costing study [9]. Visible outliers will be reconfirmed with individual hospital contacts before determining median costs among all centers for each variable in the dataset to be used for all primary and secondary analyses. Data from sites that have cost accounting methodologies precluding the inclusion of certain data will be noted, but multi-country median costs will be used to improve the generalizability of our estimates and to mitigate the influence of high and low cost outliers. Prior to final analyses being undertaken, participating sites will be re-queried to determine if particular costs have changed substantially (for example, by more than 25%), beyond inflationary or deflationary changes, over the course of the study and if so, the most current costs will be used. Country and year-specific costs will be converted to US dollars, first accounting for annual inflation [22–25]. We plan on using international currency conversion, instead of purchase power parity (PPP)-based conversions, because health-specific PPPs are not available for all participating countries, and non-health PPP conversion rates vary substantially over the period of the analysis [23]. Country-specific costs will be considered only in sensitivity analyses. As of 1 June 2013, 1 United States dollar was worth approximately 1.03 Canadian dollars, 1.04 Australian dollars, 2.12 Brazilian Real, and 3.75 Saudi Arabian Riyal [23].

### E-PROTECT analytic plan

The base case cost-efficacy ratio is the ratio of incremental costs per incremental effects of LMWH versus unfractionated heparin during the period of hospitalization. Incremental costs will be derived for all patients by first calculating total costs for all patients in each arm of the PROTECT trial. Item costs will be multiplied by the frequency or event rates for medications administered, laboratory and radiological tests incurred, other diagnostic or therapeutic procedures performed, transfusions received, per day personnel and ICU or ward costs, depending upon number of events and length of stay in the ICU and hospital. Total, then median and mean per patient costs for each of the LMWH and unfractionated heparin groups will be calculated. Incremental costs will be taken as the difference in median per patient costs between groups; however, mean costs will also be provided in order to generate total costs. Effects for the base case analysis will be calculated separately for each primary (all thromboses), secondary (PE, DVT, major bleeding and HIT) and tertiary (survival) endpoints. Incremental effects will be taken as the difference in per patient event rates between groups. Therefore cost-effectiveness ratios will be displayed in terms of incremental costs divided by incremental effects, specifically, the cost to prevent a thrombosis at any site, the cost to prevent a PE, DVT, major bleeding event and episode of HIT, and life-year gained as is commonly used in cost-effectiveness analysis for VTE prevention strategies (Box 2) [6]. If costs are less in the LMWH group, a cost-minimization analysis will be reported, highlighting the difference in costs (with 95% confidence intervals) between groups.

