## Background

Venous thromboembolism (VTE) is a common complication of critical illness and has important clinical consequences, including deep vein thrombosis (DVT), pulmonary embolism (PE), increased length of stay in the intensive care unit (ICU) and hospital and death [1–3]. Although DVT has potentially serious consequences, it is often unrecognized in the ICU as the clinical examination for DVT lacks sensitivity and specificity [4]. Further, routine ultrasound screening for DVT is not a cost-effective diagnostic strategy in practice [5]. Thus, thromboprophylaxis is the most appropriate mechanism to prevent VTE and its complications among critically ill patients.

We have previously documented that most economic evaluations of VTE strategies are designed after the results of the trial are known, and are funded by the manufacturers of the agents compared [6]. This introduces the opportunity for biased design and interpretation of economic evaluations. Therefore, we designed the economic evaluation (E-PROTECT) of a multicenter randomized, blinded controlled trial of 3,746 patients comparing the effectiveness of unfractionated heparin (UFH) and low molecular weight heparin (LMWH) (dalteparin) [7]. The primary objective of E-PROTECT is to identify and quantify the total (direct and indirect, variable and fixed) costs associated with the management of critically ill patients participating in the PROTECT trial, and to combine costs and outcome results to determine the incremental cost-effectiveness of LMWH versus UFH, from the acute healthcare system perspective, over a data-rich time horizon of the ICU admission and hospital admission.

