### Evaluation Framework Overview

**Question**: Is the use of LMWH as compared to UFH cost-effective for the prevention of VTE in critically ill medical-surgical patients?**Perspective**: Our primary perspective is the acute healthcare system perspective. We will perform sensitivity analyses from various geographic regions participating in the PROTECT trial.**Clinical outcomes**: Rates of all thromboses, DVT, PE and complications (for example, bleeding and HIT), length of stay and mortality (ICU and hospital).**Costs**: All direct and indirect medical costs associated with treatment and complications (such as ICU and non-ICU hospitalization, personnel, medications, diagnostic testing and procedures) will be identified and evaluated. Costs will be converted to Canadian and United States (2013 dollar rates) costs.**Evaluation**: Our primary outcome is the incremental cost per in-hospital thrombotic event avoided. Long-term results will be presented in terms of costs per life year and quality-adjusted life years gained, using utilities from studies of appropriate duration, to allow for broad comparison of cost-efficacy with other medical interventions.**Comparators**: We will compare LMWH with UFH for outcomes and associated costs.**Time horizon**: We will focus on near-term horizons; costs and incremental cost effectiveness ratio outcomes at ICU and hospital discharge. We will model long-term outcomes over a lifetime horizon.**Discounting**: We will discount cost and utilities at 3% for any longer-term (over one year) analyses.**Uncertainty**: We will use sensitivity analyses and bootstrapping to produce confidence intervals.

DVT = deep vein thrombosis; HIT = heparin induced thrombocytopenia; ICER = incremental cost-effectiveness ratio; ICU = intensive care unit; LMWH = low molecular weight heparin; PE = pulmonary embolism; UFH = unfractionated heparin; VTE = venous thromboembolism.

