## Discussion

The PROTECT trial is the largest trial undertaken of VTE prophylaxis for critically ill patients. Although LMWH has been shown to be an effective means of VTE prophylaxis for many patient populations, it has historically been associated with a higher drug acquisition cost than UFH, and the relative effects, side-effects and broader costs of VTE prophylaxis are unknown. A prospective economic evaluation is critical to the interpretation of the results of the PROTECT trial. The PROTECT trial results suggest that LMWH may reduce the frequency of pulmonary embolus and heparin-induced thrombocytopenia. Thus, physicians, pharmacists and policy makers will need to know whether the cost provides good value for the healthcare dollar. An economic evaluation is still critical for alternative clinical outcomes, particularly for differences in the adverse event profile between treatments that may lead to additional resource consumption. E-PROTECT provides an opportunity to answer these questions and address the cost-efficacy of VTE prevention using results with minimal risk of bias.

In preparation for E-PROTECT, we have performed a number of preliminary and sub-studies, including a systematic review of the VTE economic evaluation literature to inform cost-drivers, the E-PROTECT pilot study in three countries to determine feasible and valid cost data collection, and we have developed a decision-analytic model to explore both the importance of protocoled screening versus clinical case finding for VTE, and evaluate the long-term outcomes of various detection and treatment strategies [5, 6, 9].

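### The primary cost-effectiveness ratio divides a difference in median costs by a difference in event rates, so it is not a cost per thrombosis avoided

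*Protocol article*

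**What the plan says.** All of this comes from the protocol article.

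- **Numerator** (E-PROTECT analytic plan): "Incremental costs will be taken as the difference in median per patient costs between groups". The same sentence adds that "mean costs will also be provided in order to generate total costs".
- **Denominator** (same section): "Incremental effects will be taken as the difference in per patient event rates between groups".
- **Use** (Evaluation Framework Overview): "Our primary outcome is the incremental cost per in-hospital thrombotic event avoided". The secondary ratios for PE, DVT, major bleeding and HIT have the same form.
- **Objective** (Background): "to identify and quantify the total (direct and indirect, variable and fixed) costs associated with the management of critically ill patients", and to combine costs with outcomes from the acute healthcare system perspective.
- **A step that depends on the sign of the cost difference** (E-PROTECT analytic plan): "If costs are less in the LMWH group, a cost-minimization analysis will be reported".

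No other section replaces the median by the mean in the ratio. The medians under Exploring cost variability among sites are a separate matter: they are unit prices taken across hospitals. The Statistical analyses section says only that means or medians will describe costs.

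**The concern.** A proportion of patients with an event is a mean, so the denominator is a mean difference. The numerator is not. Total spending in an arm equals the number of patients times the mean cost. It does not equal the number of patients times the median cost, unless the two happen to coincide. A payer who wants the extra spending per thrombosis prevented needs extra total cost over extra events, and that is a ratio of mean differences. A median difference over a rate difference cannot be multiplied back into either.

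The choice matters here because treatment may act on cost through two different routes. A drug-price difference is borne by nearly every patient. The Discussion also says that "LMWH may reduce the frequency of pulmonary embolus and heparin-induced thrombocytopenia", and those are events in a minority of patients that may be expensive. Medians and means weigh these two routes differently. The result feeds the primary outcome. The direction of the cost difference also bears on whether a cost-minimization analysis is reported and, under the sections on post-discharge modelling and Discussion, on whether long-term modelling and a willingness-to-pay study follow.

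**Working it through.** The article states no cost, event rate or variance, so there is no figure of its own to reproduce. Every dollar amount, risk and skewness value below is an assumption. Only the trial size of 3,746 is from the article. I assume 1:1 allocation, so 1,873 per arm.

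**1. Totals.** For log-normal costs, median/mean = exp(-s²/2), where s is the SD on the log scale:

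| s | median/mean |
|---|---|
| 0.8 | 0.73 |
| 1.0 | 0.61 |
| 1.2 | 0.49 |

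The number of patients times the median would recover only about half to three-quarters of total spending.

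**2. Difference in means.** Let d be the extra drug cost per LMWH patient, r the absolute risk reduction and C the cost per event. Then mean difference = d - r × C. This holds wherever in the cost distribution the events fall.

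**3. Worst case: events only in stays already above the median.** Adding or removing cost above the median leaves the median where it was, so median difference = d. Take d = $100, r = 0.01, C = $40,000:

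- Mean difference: 100 - 0.01 × 40,000 = **-$300** per patient (LMWH saves).
- Median difference: **+$100** per patient (LMWH costs more).
- Per event avoided: -300/0.01 = -$30,000 (LMWH dominant) against +100/0.01 = +$10,000.

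**4. Opposite case: events independent of baseline cost.** The median solves (1-p)F(x) + pF(x-C) = 0.5, where F is the baseline distribution and p the event risk. With baseline median $40,000 and risk falling from 2% to 1%:

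| s | C | d | Mean difference | Median difference |
|---|---|---|---|---|
| 0.8 | $20,000 | 0 | -$200 | -$246 |
| 0.8 | $40,000 | 0 | -$400 | -$420 |
| 0.8 | $60,000 | 0 | -$600 | -$420 |
| 1.0 | $30,000 | $100 | -$200 | -$318 |
| 1.0 | $30,000 | $400 | +$100 | -$18 |

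Here the median mostly over-counts the averted cost. It can also under-count it when an event is very expensive relative to the spread (third row). The signs usually agree. They can still reverse once a drug-price difference is included, and in the last row the reversal favours LMWH, the opposite of step 3.

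**5. Sampling error (s = 0.9, median $40,000).**

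- Mean cost = 40,000 × exp(0.405) = $59,972. SD = 59,972 × √(exp(0.81) - 1) = $66,995.
- SE of the mean difference = 66,995 × √(2/1,873) = about $2,190. Simulation gave about $2,180.
- SE of the median difference = [40,000 × 0.9 × √(2π)/2] × √(2/1,873) = 45,119 × 0.0327 = about $1,474. Simulation gave $1,450 to $1,470.

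The $400 gap in step 3 is about 0.18 of one SE of the mean difference (400/2,180). At a 1-point risk reduction that gap is worth $40,000 per event avoided, and one SE is worth about $218,000.

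**The case against.** The best defence is that the means are not withheld. The analytic plan computes total, mean and median per-patient cost in each arm, so a reader can form the mean difference from planned output. This stands. A reader might infer that the total-cost objective itself is contradicted, but the documents do not support that, since totals are to be generated from means. What remains is that the headline ratio is defined on the median.

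A second defence is that medians resist outliers and give a tighter interval. Outlying hospital prices are already handled by median unit prices across sites. A very expensive patient is real spending by the payer, not an error to be damped, and a tighter interval around a different quantity is no gain.

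Third, a reader might infer that the plan will show LMWH as dearer when it saves money. The documents do not support that either. The reversal in step 3 follows from confining every event to above-median stays, which no section states. The Discussion notes that proximal leg DVT in these patients is usually asymptomatic, and DVT is part of the primary effect. Under independence the distortion mostly runs the other way.

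Fourth, moving to means does not secure the sign. With a true difference of -$300 and an SE of $2,180, the estimated mean difference would be positive about 45% of the time. For the same reason, disagreement in sign between sample means and sample medians is not evidence of the mechanism. In simulated trials of this size it occurred about 30% of the time or somewhat more, even with no treatment difference at all.

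Finally, the cost-minimization sentence, the subgroup cost differences and the bootstrap cost-effect pairs do not name the median. That they inherit it is an inference. They need a clarifying statement rather than a correction.

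**Conclusion.** The point holds as a mismatch of estimand in the base-case ratio. The numerator is fixed as a median difference and the denominator is a mean difference, so the primary ratio and each secondary ratio of the same form are not costs per event avoided. This conclusion needs no assumed figures beyond skewed costs.

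The size and the direction of the distortion cannot be derived from the article. In the illustrations the two cost differences lie from about $20 to $400 per patient apart, in either direction. Sign reversal is possible under both event patterns examined, is assured by neither, and is small against sampling error. The reason to change is that the plan should estimate the quantity it names. Because this defines the primary outcome, it should be corrected before the analysis.

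**What to change.** Replace the sentence that defines incremental cost with:

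> Incremental cost is the difference in arithmetic mean per-patient cost (LMWH minus UFH), with a bootstrap 95% confidence interval.

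Use it in the base-case ratio and in all secondary ratios. State that the cost-minimization trigger, the subgroup cost differences and the bootstrap cost-effect pairs use this same mean difference. Keep medians and interquartile ranges as description only.

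The cost is one sentence plus one clarification. Mean costs are already to be calculated, and Trial status says that costing is not complete. The downside is a wider interval: an SE of about $2,180 instead of $1,450 to $1,470 under the assumptions above.

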### E-PROTECT sensitivity analyses

As patient characteristics, effects and costs may differ outside of tightly controlled clinical trials and in various jurisdictions, we plan a number of sensitivity analyses to explore how incremental cost-effectiveness ratios may change with plausible differences in values, including costs of LMWH and UFH, and per day cost of care in ICU and hospital wards. We will also perform sensitivity analyses using the efficacy analysis of the PROTECT trial that considered only patients who received the study drug for two days or more and had two or more leg compression ultrasounds, and by considering only symptomatic thromboses. Multi-way sensitivity analyses will be performed by varying the estimates of pairs of potentially influential variables. We will perform a probabilistic sensitivity analysis of pairs of known costs and effects from the PROTECT trial, using bootstrapping techniques, among 1,000 samples, with replacement, in order to generate an incremental cost-effectiveness plot [26, 27].

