### Secondary analyses

#### E-PROTECT post-hospital discharge modeling

Some clinical events may occur after ICU and hospital discharge and these events may utilize resources (such as re-admission to the ICU, rehabilitation and physician visits). Because we cannot follow all patients in the PROTECT trial over their actual life expectancy, we may use discharge vital statistics and known post-critical illness follow-up literature to model the lifetime effects and cost-efficacy ratios of prevention strategies for all patients in the PROTECT trial, depending upon the results for the in-hospital time horizon. We will know clinical events and outcomes until death or discharge from hospital. However, if the primary analysis implies that long-term effects and costs are important to explore (particularly if the primary analysis demonstrates one strategy is more costly but with greater effects), post-discharge, a Markov-based process (Figure 1) will be used to model longer-term events and will allow patients to transition between states of health or illness until all patients in the model have died [5].

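### A lower observed LMWH cost alone triggers a cost-minimization analysis, with no condition on effects and no counterpart for UFH

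*Protocol article*

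**What the plan says.** Under E-PROTECT analytic plan, the base case is a ratio: "The base case cost-efficacy ratio is the ratio of incremental costs per incremental effects of LMWH versus unfractionated heparin during the period of hospitalization". Its two parts are defined in the same section. For costs, "Incremental costs will be taken as the difference in median per patient costs between groups"; for effects, "Incremental effects will be taken as the difference in per patient event rates between groups". Evaluation Framework Overview and Outcomes Overview agree on the primary outcome: "Our primary outcome is the incremental cost per in-hospital thrombotic event avoided".

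The analytic plan section then closes with a conditional rule: "If costs are less in the LMWH group, a cost-minimization analysis will be reported, highlighting the difference in costs", with a 95% confidence interval. The article gives no rule for the case in which UFH is the cheaper arm.

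Three other places bear on the rule:
- E-PROTECT sensitivity analyses plans resampling of cost and effect pairs, "using bootstrapping techniques, among 1,000 samples, with replacement, in order to generate an incremental cost-effectiveness plot".
- E-PROTECT post-hospital discharge modeling foresees lifetime modelling, "particularly if the primary analysis demonstrates one strategy is more costly but with greater effects".
- The Discussion says of the clinical results: "The PROTECT trial results suggest that LMWH may reduce the frequency of pulmonary embolus and heparin-induced thrombocytopenia".

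**The concern.** Cost-minimization leaves effects out of the comparison. That is defensible when effects have been shown, or are agreed, to be equivalent. Here the analysis is started by an observed cost difference, which carries no information about effects. Nothing in the article makes equivalence or non-inferiority for thrombosis, bleeding or HIT a precondition.

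A lower LMWH cost covers two opposite findings. With fewer events, LMWH is dominant. With more events, the saving is bought with extra thromboses or bleeds, and a decision maker has to weigh one against the other. The rule highlights the same figure under the same label for both.

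It is also one-sided. The Discussion ties the follow-up study of willingness to pay to LMWH being the costlier arm, so that study would not cover a cheaper, less effective LMWH either. The Background presents advance planning as protection against biased design and interpretation, and a rule that applies only in favour of one arm sits badly with that aim.

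**Working it through.** The plan gives no figure to reproduce on this point. The check is mainly one of logic, followed by two illustrations.

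**Step 1: what the rule and the ratio each distinguish.** Let ΔC = LMWH cost minus UFH cost per patient, and ΔE = events avoided per patient = UFH event rate minus LMWH event rate. The ratio is ΔC/ΔE. The values of ±$50 and ±0.01 are invented to show the signs.

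| Finding for LMWH | ΔC | ΔE | ΔC/ΔE | Rule applies? |
|---|---|---|---|---|
| Cheaper, fewer events (dominant) | −50 | +0.01 | −5,000 | yes |
| Cheaper, more events (trade-off) | −50 | −0.01 | +5,000 | yes |
| Costlier, fewer events (trade-off) | +50 | +0.01 | +5,000 | no |
| Costlier, more events (dominated) | +50 | −0.01 | −5,000 | no |

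The rule puts rows 1 and 2 together. The sign of the ratio puts row 1 with row 4 and row 2 with row 3. Neither the cost-only result nor the ratio alone identifies the finding; the two differences have to be read together.

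**Step 2: is equality of effects assumed anywhere?** No. The analytic plan estimates an effect difference, the primary outcome divides by it, and the Discussion suggests that PE and HIT differ in favour of LMWH.

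**Step 3: how small an effect difference matters.** The section on the pilot study reports ratios in the literature ranging from dominance of LMWH to under $5,000 per VTE avoided. Take $5,000 as an assumed value per event; it is not a threshold set by the plan. Net benefit per patient = saving − 5,000 × extra event rate, so the break-even extra rate is saving/5,000:
- $25 saving: 25/5,000 = 0.5 percentage points
- $50 saving: 50/5,000 = 1 point
- $100 saving: 100/5,000 = 2 points
- $500 saving: 500/5,000 = 10 points

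With a $50 saving and 2 points more thromboses, net benefit is 50 − 5,000 × 0.02 = −$50, while the cost-only result shows a $50 advantage. For large savings, plausible effect differences matter little at this value.

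**Step 4: could a non-significant effect difference stand in for equivalence?** Inputs: 3,746 patients (The PROTECT trial), taken as 1,873 per arm; alpha 0.05 (Statistical analyses), taken as two-sided; thrombosis rates of 5% to 12%, assumed because the article gives none.
- 95% CI half-width = 1.96 × √(2p(1−p)/1,873). At p = 0.05 it is 1.4 points; at p = 0.12 it is 2.1 points.
- Power to detect a 2-point excess = Φ(0.02/SE − 1.96), with SE = √[(p₁(1−p₁) + p₂(1−p₂))/1,873]. For 5% against 7% it is about 73%; for 12% against 14%, about 44%.

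An excess of 1 to 2 points could go undetected, so a non-significant effect result would not justify a cost-only comparison.

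**The case against.** The strongest reply is that nothing is lost. The sentence says that the cost-minimization result is reported; it does not say that it replaces anything. The ratios are to be displayed for every endpoint, the primary outcome is stated without condition, event rates are listed as clinical outcomes, and the bootstrap plot is planned whichever arm is cheaper. All of this stands. A reader might infer that joint cost-effect uncertainty is dropped, or that the form of the primary result switches with the data. The text does not support either inference.

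Second, the wording on post-discharge modelling is symmetric. UFH costlier with fewer events is the same finding as LMWH cheaper with more events. So the trade-off is partly covered, though that section says both that modelling may be done and that it will be, depending on the in-hospital results.

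Third, the Discussion points to fewer PE and HIT events with LMWH. For those outcomes a lower LMWH cost would mean dominance, so the fault would be a wrong label and not a concealed harm. The article gives no direction for all thromboses or major bleeding, so the trade-off is not excluded there.

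Fourth, an article may leave an equivalence margin to a fuller document. That is fair, and the absence of a margin is not the fault by itself. But the article does state the trigger, and the trigger is cost alone.

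**Conclusion.** The point holds as a fault in a stated decision rule. Cost-minimization is started by lower LMWH cost without regard to effects, for one arm only, in a plan that elsewhere estimates effects and expects some to differ. The consequence is one of labelling and emphasis: the highlighted result cannot tell dominance from a trade-off, although the material needed to do so is planned elsewhere in the article.

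A reader might want to say how often chance alone would set off the rule. The documents give no cost distribution, and the chance of a lower observed LMWH cost is not the chance of lower cost with more events, so no such figure is offered. The dollar and precision figures in the working are illustrations. They rest on the assumed value per event, equal allocation, a two-sided alpha and assumed thrombosis rates. The conclusion itself depends on none of them. This should be fixed before the final analysis; it does not undermine the primary outcome.

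**What to change.** Delete the cost-minimization sentence. In its place, state that whichever arm is cheaper:
- the cost difference and the effect difference are reported together, each with its 95% CI;
- the share of the 1,000 bootstrap pairs in each quadrant of the cost-effectiveness plane is given, using the same cost measure as the base case;
- LMWH is described as dominant if it is cheaper with fewer events, and the result is given as a saving per additional event if it is cheaper with more events, with mirror wording for UFH.

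If net monetary benefit is added, show it over a range of values per event, because the Discussion says that no clear threshold exists for avoiding a VTE event.

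The change needs no new data. The bootstrap pairs are already planned, so the added work is counting quadrants, an interval for the effect difference and a few sentences of text. Trial status says that costing was incomplete at submission, so the rule could still be changed then. Whether incremental cost should be a median or a mean difference is a separate question, which this change leaves open.
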